### **2.4 Potential Risks and Benefits**

#### **2.4.1 Potential Risks**

tPCS may cause discomfort or tingling sensation to some people. Some people may have skin redness due to allergic reaction to electrode. Few people may complain of headache post stimulation. Otherwise, there is minimal risk in tPCS if there are no contraindication.

#### **2.4.2 Potential Benefit**

A significant portion of children with ASD have unmet medical needs that are not adequately addressed by behavioral therapies and certain medications. Use of tPCS may be potentially an effective novel intervention for children with ASD to improve the core symptom of social functioning without potential drug side effects, and with modulating aberrant brain activity such as disrupted E/I balance may offer treatment beyond symptom management. Additionally, tPCS may be effective to treat sleep dysfunctions which are a common comorbidity in ASD, this may reduce caretaker burnout and improve quality of life for the child and the entire family.

## **3 Study Population**

### **3.1 Number and Nature of Subjects to be Enrolled**

340 children with ASD, aged 3 to 14 years old will be enrolled for this study. See section 9.1 for detailed sample calculation.

### 3.3 Screening Visits Procedures and Recruitment

Potential participants will be children with ASD coming for clinic visit and receiving inpatient and outpatient pediatric psychiatry, neurology and/or ASD therapy services at the eight sites. The study team doctors on duty will be responsible for identifying potential participants and screened according to the diagnostic, inclusion and exclusion criteria as stated in sections 3.4 to 3.6. Screening per participant will take approximately two hours. If criteria are met, potential participants and their parents /legal guardian who show interest in the study will be given relevant information (standard study participation information sheet ) and the consent /assent form (See Appendix 4) in a private room which is comfortable and with privacy to consider carefully. Adequate time will be given to the participant to consider participation. There will be no coercion. Any query will be redirected to the study team doctor on site. Subjects and parents / legal guardians will be informed that participation or not will not affect medical care. If the child has some but not full understanding of the information sheet & consent form, the simplified version (assent form) will be used. However, assent form (between 6 – 14 years old) is omitted if subject is unable to read and understand due to chronic ASD condition. Consent will be taken by anyone from the study team on site. Parents/ legal guardian will sign the consent form in the presence of a witness.

### 3.4 Diagnostic Criteria

Diagnosis of ASD according to DSM-V (2013) criteria published in the United States and do not have worse than moderate-to-severe intellectual disability according to the Wechsler Intelligence Scale for Children, 4th Edition (WISC-IV). Diagnosis of ASD will be performed by trained child psychiatrists in each site with at least 5 years of experience. Assessment of intellectual disability will be performed by educational specialists with at least 3 years of experience.

### 3.5 Inclusion Criteria

- A. Subject meets the DSM-V diagnostic criteria for autism spectrum disorder.
- B. The subject and parents of the subject gave informed consent to the treatment, agree to commit to the course of treatment and complete the various pre- and post-treatment assessments.
- C. Children aged 3-14 years, regardless of gender.
- D. Subjects with IQ score > 35 , no worse than moderate intellectual disability, according to WISC (4th edition)

E. No history of epilepsy.

### 3.6 Exclusion Criteria

- A. Those who do not meet the above inclusion criteria;
- B. Subjects <3 years or >14 years old;
- C. Subjects with IQ score  $\leq 35$  , according to WISC (4th edition)
- D. Subjects with comorbid epilepsy or history of epileptic disorders
- E. Subjects with presence of severe psychiatric disorders such as schizophrenia and psychosis, or a family history of schizophrenia and psychosis.
- F. Subjects diagnosed with obstructive sleep apnea.
- G. Subjects with skull defect or presence of severe scalp infection at the proposed site of stimulation.
- H. Subjects with a history of craniotomy, presence of any ferromagnetic metal or implanted medical devices in the head or body, e.g. cochlear implant, pacemaker or defibrillator, history of severe neurological disorders such as brain tumors and intracranial infection
- I. Subjects with history of substance abuse or dependence, use of benzodiazepines, neuroleptics and antipsychotic medications including risperidone and haloperidol.
- J. Subjects who have current involvement with other forms of non-invasive brain stimulation including transcranial magnetic stimulation or transcranial direct current stimulation.

### 3.7 Drop-out Criteria

- A. Subjects that withdrew midway due to adverse events
- B. Subjects where treatment was interrupted for more than 7 days during the study, due to sickness such as acute respiratory tract infection.
- C. Subjects who failed to complete the course of treatment due to poor compliance or unexpected changes in parents' demands.
- D. Subjects whose circumstances no longer adhere to the inclusion and exclusion criteria midway through the trial, Eg. non-compliance of treatment protocol, subjects who begin a drug or treatment course in the exclusion criteria, without informing the study team.
- E. Cases where significant human errors were involved including administration of incorrect treatment dose and not being assessed according to the evaluation standards set in this trial during the pre- and post-treatment assessments.
- F. Subjects with significant missing items in the pre- and post-evaluations resulting in incomplete data.

### 3.8 Provisions for dropout cases and handling of missing data

- A. Drop-out definition: As per clause 3.6. Subjects who drop out will not be replaced.
- B. Handling of missing data: For subjects who have dropout, the researcher will contact the subjects as soon as possible to ask for the reason for the dropout and make records of the last treatment session. Post-treatment assessments will be completed using actual available data according to best effort basis, where applicable, statistical imputation and other assumptions will be made for Intention-To-Treat analysis. All relevant trial data should be properly kept on file for the dropout cases, which may be required for full analysis.

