## 9 Sample Size and Statistical Methods

### 9.1 Determination of Sample Size

Based on a two-sided paired t-test at 80% power, 5% one-sided alpha and an expected effect size of small (0.20) when using bilateral frontal montage and medium (0.52) when using prefrontal-cerebellar montage, we will use an average of 0.36 effect size to compute the sample size, which leads to 120 per group. Based on an estimated 40% drop-out rate due to potential implications from post- COVID heightened travelling restrictions in Guangdong province, a sample size of 339 is required. We will use 340 as the sample size for recruitment in this study.

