### 9.2 Statistical and Analytical Plans

#### 9.2.1 General Considerations

Statistical analysis will be implemented using the IBM SPSS version 27.0. Before applying any statistical test, the data sets will be tested for a normal distribution with the Shapiro–Wilk test. If the data was found to be normally distributed, then one- way analysis of variance ANOVA and Student’s t-test will be used for the comparison between groups. Analysis of Covariance ANCOVA will be used to compare one or more means between groups

while controlling for the effects of one or more covariates (continuous variables that are related to the dependent variable). For comparison with the baseline value, paired t-test or one-way analysis of variance (ANOVA) will be used to compare the differences within the group before and after treatment. If the data was found to be not normally distributed then Kruskal-Wallis test or Mann-Whitney rank-sum test was used for the comparison. In order to correct for multiple comparisons, Bonferroni correction will be used to further validate the significance of each p-value. All statistical tests were conducted using a two-sided test. The  $\alpha$ -value was set to 0.05 for all the statistical tests and < 0.01 for Bonferroni correction. Chi-Squared test was used for categorical data, and Mann-Whitney rank sum test was used for ordinal data.

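### The 80% power in section 9.1 is for 120 analysable children per group at the full 0.36 effect; it is not established for an intention-to-treat analysis of 340 children with 40% dropout

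*Combined protocol and SAP*

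**What the plan says.** Section 9.1 (Determination of Sample Size) averages two effect sizes, 0.20 and 0.52, and continues: "we will use an average of 0.36 effect size to compute the sample size, which leads to 120 per group". It then enlarges the total: "Based on an estimated 40% drop-out rate" gives 339, rounded to 340. Section 4.2 splits this into 170 per group. The Protocol Deviations note at the front gives the expected dropout as a range, 30% to 40%.

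Section 3.8 says that dropouts are not replaced and that their post-treatment assessments are completed as far as possible. It adds that "where applicable, statistical imputation and other assumptions will be made for Intention-To-Treat analysis". This is the only place where an efficacy analysis population is named. Section 9.2 names neither a primary analysis set nor an imputation method.

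Section 3.7 defines dropout. Several criteria concern lost treatment, for example "Subjects who failed to complete the course of treatment due to poor compliance". Others (F, and part of E) concern missing items or assessment errors.

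**The concern.** The sizing treats dropouts as removed and gives everyone who remains the full effect. An intention-to-treat analysis keeps the dropouts. The treatment is a course of 20 weekday site visits, and 9.1 attributes the expected dropout to travel restrictions, so many dropouts would plausibly miss sessions. If they benefit less, the average effect across all randomised children is below 0.36 and the 80% does not carry over.

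Two things are at stake. A non-significant intention-to-treat result could be over-read as evidence of no effect, because readers would believe the trial had 80% power. And with no primary set fixed in 9.2, analysts could fall back on completers to recover the planned power, which gives up the randomised comparison.

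**Working it through.** **Inputs.** Effect 0.36 with SD 1, 120 per group, 80% power, 40% dropout, 340 enrolled (9.1); 170 per group (4.2); 30% as the lower dropout figure (Protocol Deviations). Section 9.1 contradicts itself on the test: "Based on a two-sided paired t-test at 80% power, 5% one-sided alpha". Section 9.2.1 settles sidedness for the analysis: "All statistical tests were conducted using a two-sided test", at 0.05. I use a two-sample t-test, two-sided 5%.

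**Reproducing 120 per group.** n = 2(1.960 + 0.842)² / 0.36² = 121.1, so 122 per group (t-test: 122.1). Power at 120 per group is 79–80%. The alternatives do not fit: two-sample one-sided 5% gives 96; a paired test gives 63 (two-sided) or 49–50 (one-sided). So 120 is in effect a two-sample, two-sided 5% figure for children with analysable data.

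**Reproducing 339.** 242 × 1.4 = 338.8, so the total was multiplied by (1 + 0.4). Leaving 240 after 40% dropout would need 240 / 0.6 = 400.

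**Completers actually left.** 340 × 0.6 = 204, or 102 per group. At 0.36, the expected test statistic is 0.36 × √(102/2) = 2.57 and power is about 73%. This needs no assumption about the effect in dropouts. Missing-at-random imputation adds little information, so it gives roughly the same. At 30% dropout, 340 × 0.7 = 238, or 119 per group, and power is about 79%.

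**Intention-to-treat with everyone assessed.** With d the dropout share (equal in both arms) and r the share of the effect that dropouts keep, the average effect is 0.36 × (1 − d + d·r). With 170 per group:

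| r (assumed) | Effect, d = 40% | Power | Effect, d = 30% | Power |
|---|---|---|---|---|
| 0% | 0.216 | 51.0% | 0.252 | 63.9% |
| 25% | 0.252 | 63.9% | 0.279 | 72.7% |
| 50% | 0.288 | 75.4% | 0.306 | 80.3% |
| 75% | 0.324 | 84.6% | 0.333 | 86.5% |
| 100% | 0.360 | 91.1% | 0.360 | 91.1% |

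**Break-even.** 80% power with 170 per group needs an average effect of 0.305. At 40% dropout, r = (0.305/0.36 − 0.6)/0.4, about 62%. At 30% dropout, r = (0.305/0.36 − 0.7)/0.3, about 49%.

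**Dilution and missing outcomes together.** If r = 0 and the precision is only that of 102 per group, the expected statistic is 0.216 × √(102/2) = 1.54 and power is about 34%.

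**Is this only the inflation arithmetic?** No. With 200 per group and 40% dropout, power at r = 0, 25 and 50% is 58%, 71% and 82%. Enlarging to 400 would not by itself secure 80% under intention-to-treat.

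**The case against.** A reader might infer that the trial's power as analysed is 51–75%. The documents do not support that.

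- The retained effect is an assumption. The full range is 51–91%, which straddles 80%, and at 30% dropout half the effect still gives about 80%.
- Dropout is not the same as no treatment. Criterion F and the assessment-error part of E can apply to fully treated children, and nothing is said about when children drop out.
- Section 3.8 expects best-effort data plus unspecified imputation, not 340 observed outcomes. Full observation is therefore neither the expected case nor a dependable bound: depending on the imputation, power could be about 73%, or as low as about 34%.
- Intention-to-treat appears once, in a missing-data clause with a qualifier. It is too strong to say that the plan formally makes it primary.
- The documents do not say whether the two source effect sizes already include non-adherent children.
- Alpha is itself unsettled. In 9.2.1 the "value was set to 0.05 for all the statistical tests and < 0.01 for Bonferroni correction". At 0.01, power for r = 0 to 50% at 40% dropout would be about 28–53%; at one-sided 5%, about 64–84%.

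All of this stands, and it rules out any single replacement figure. It does not rescue the 80%. No other efficacy population is named, 9.1 contains no dilution term, and the completers route also falls short at the planned dropout.

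**Conclusion.** The concern holds in a limited form. The 80% belongs to 120 analysable children per group at the full effect, and the plan does not show that it applies to the one population it names. The firmest figure is about 73%, for the 102 completers per group left at 40% dropout; it rests only on the plan's own inputs and a two-sided 5% test. The intention-to-treat range of 51–91% (64–91% at 30% dropout) also rests on equal dropout in both arms, full outcome follow-up, and an assumed retained effect from 0 to 100%. Within it, 80% is reached only if dropouts keep about 62% of the effect (about 49% at 30% dropout). Missing outcomes could take power lower.

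**What to change.** Reword section 9.1:

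1. State that the primary analysis is intention-to-treat on all randomised children.
2. Label the 80% as the power for 120 completers per group at 0.36.
3. State that 340 enrolled with 40% dropout leaves about 102 completers per group and about 73% power. Without this line, the 120 label would imply completers that the trial is not expected to have.
4. Replace the single 80% claim with intention-to-treat power over the whole 0–100% retained-effect range: 51–91% at 40% dropout and 64–91% at 30%. Label it as assumption-based and conditional on full outcome follow-up.

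This is wording only, with no change in enrolment. The cost is a less favourable power statement.

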## 4 Study Design

The trial design will be a multi-center, double-blind, sham-controlled, parallel group, randomized 1:1 clinical trial involving eight hospitals in China.

[figure not shown]

### 4.1 Randomization - Allocation Sequence Generation

Centralized randomization and allocation will be conducted in accordance with China standards in “Methodology of Clinical Scientific Research of Integrated Traditional Chinese and Western Medicine (2nd edition)”. Recruitment of study subjects will be performed locally at the eight sites, details of recruited subjects will be sent within the same day by Phone/WeChat/Email to an administrator at the main site, Nanhai Maternity and Children’s Hospital, who is uninvolved in the treatment, outcome assessment or final data analysis. The administrator will enter the participant’s details into a secure centralized database. A random allocation sequence will be generated using IBM SPSS27.0 statistical software for 1:1 group division into active-tPCS/ intervention

Group and sham-tPCS/ control Group. 340 random numbers and their corresponding group allocation will be put into 340 opaque, sealed, and identical envelopes. The group allocation will only be marked on the inside of the envelopes.

## 4.2 Randomization - Allocation Implementation

Subjects who meet the inclusion criteria and have signed consent form will be numbered according to their sequence of the time of visit (from 1 to 340). The administrator will send out the envelope with number corresponding to the number of the subject to the respective hospital of the subject. Upon opening of the envelope, the group allocation is revealed, and the subject is randomized to either the Control (Sham-tPCS) Group or the Intervention (active-tPCS) Group, with 170 subjects in each group.

## 4.3 Study Visits and Procedures

| Visit to Site                                                                                                                                | Visit 1             | Visit 2-21          | Visit 22                  |
|----------------------------------------------------------------------------------------------------------------------------------------------|---------------------|---------------------|---------------------------|
| Timeline                                                                                                                                     | Week 0              | Week 1-4            | Week 4                    |
| Procedure                                                                                                                                    | Baseline assessment | Intervention Period | Post-treatment assessment |
| Informed Consent                                                                                                                 | X                   |                     |                           |
| ATEC 2 ,                                                                                                                          | X                   |                     | X                         |
| ABC  ,                                                                                                                           | X                   |                     | X                         |
| CSHQ 4 ,                                                                                                                          | X                   |                     | X                         |
| WISC 5                                                                                                                            | X                   |                     |                           |
| Urine test                                                                                                                                   | X                   |                     | X                         |
| Real-tPCS 6 + 1 Hour Standard Therapy 7

or

Sham-tPCS 6 + 1 Hour Standard Therapy 7 |                     | X                   |                           |

### Informed Consent

Taken at screening visit, i.e. on the same day as when they are identified as a potential participant. Randomization will be performed as per section 4.1 and 4.2, only after consent is taken (See Appendix 4).

### Autism Treatment Evaluation Checklist (ATEC)

ATEC is developed by the Autism Research Institute and designed as a one-page checklist. Comprising 77 items, the ATEC has been utilized to assess the efficacy of interventions by measuring changes in response to various treatment modalities for children with ASD. The ATEC consists of four subscales totaling 77 items:

- Scale I: Speech, Language, and Communication (14 items, with scores ranging from 0 to 28)
- Scale II: Sociability (20 items, with scores ranging from 0 to 40)
- Scale III: Sensory and Cognitive Awareness (18 items, with scores ranging from 0 to 36)
- Scale IV: Health, Physical Condition, and Behavior (25 items, with scores ranging from 0 to 75)

Each category within the ATEC utilizes a four-point rating scale to gauge the severity of issues, ranging from 0 (indicating no problem) to 3 (indicating a serious problem). The ATEC generates a total score ranging from 0 to 179, with higher scores indicating a greater degree of reported activity limitations. This comprehensive assessment tool enables researchers and clinicians to gain insight into the challenges faced by individuals with ASD and to monitor changes in symptoms and functioning over time. For this study, the ATEC will be administered twice (pre- and post-tPCS) and carried out by an experienced therapist or doctor who is blinded regarding the subject allocation.

### **3 Autism Behaviour Checklist (ABC)**

The Autism Behavior Checklist is a classic screening tool for autism. Comprising 57 items and organized into five subscales—sensory behavior, social relating, body and object use, language and communication skills, and social and adaptive skills—the checklist assigns scores ranging from 1 to 4 per item, with higher scores indicating more severe symptoms. A total score of <53 is considered a negative screening test, a total score of ≥53 and ≤67 is considered a positive screening test, and a total score of ≥68 can assist in the diagnosis of autism. In this study, the ABC will be administered twice (pre- and post-tPCS) by an experienced therapist or doctor in clinic, who is blinded regarding the subject allocation.

### **4 Children's Sleep Habits Questionnaire (CSHQ)**

The Children's Sleep Habits Questionnaire (CSHQ) is a retrospective assessment tool to investigate sleep patterns in young children consisting of 45 items designed for parents to report on their child's sleep behavior. The CSHQ covers various sleep domains, including bedtime behavior and sleep onset; sleep duration; anxiety around sleep; behavior occurring during sleep and night wakings; sleep-disordered breathing; parasomnias; and morning waking/daytime sleepiness. Each item is rated on a three-point scale: "usually" if the behavior occurred five to seven times per week, "sometimes" for two to four times per week, and "rarely" for zero to one time per week. In this study, the CSHQ will be administered twice (pre- and post-tPCS) by experienced therapists who is blinded regarding the subject allocation through interviewing parents or caregivers in clinic.

### **5 Wechsler Intelligence Scale for Children, 4th Edition (WISC-IV)**

Performed at screening visit, i.e. on the same day as when they are identified as a potential participant, those with IQ score of ≤35 is defined as having severe cognitive impairment and will be excluded from the study. The Wechsler Intelligence Scale for Children, 4th Edition (WISC- IV), is designed for use with children aged 6 to 16 years and 11 months. It provides an assessment of cognitive abilities in children within this age range, helping to identify strengths and weaknesses in various domains of intellectual functioning. An IQ score of <70 is defined as having intellectual disability.

